**Fig. 2 Fig2:**
[figure not shown]
The stepped wedge design of the IRIS study. Pregnant women will be enrolled during months 1–12 at 20–22 weeks of gestation. All midwifery practices (*n* = 60) will start with the control condition providing care as usual. At intervals of 3 months, a third of all practices will change status from the control to the intervention condition, which means providing routine third trimester ultrasound screening at 28–30 weeks and 34–36 weeks of gestation. Postnatal follow-up will be conducted in months 18–42

### Care in the intervention and control group

Both the intervention group and the control group will receive the following standard elements of midwifery care: 1) serial fundal height measurements and clinically indicated ultrasonography in line with the KNOV guideline for the detection of IUGR [26]; 2) information about life-style factors that may influence fetal development, e.g., smoking and alcohol use; and 3) advice to report a reduction in fetal movements. When IUGR is suspected, both groups will receive subsequent management based on the consensus-based protocol that will be developed in sub-study A.

### Intervention

In the intervention group two routine third trimester biometry ultrasounds will be performed, the first at 28–30 weeks of gestation and the second at 34–36 weeks of gestation. Performing two ultrasound examinations enables detection of early and late fetal growth restriction and allows monitoring of fetal growth patterns, which may reveal decreased fetal abdominal growth velocity.

### Measures

#### Baseline characteristics of pregnant women and midwifery practices

To assess comparability of study groups and predictors of outcome, data on baseline characteristics of participating midwifery practices and participating pregnant women will be collected. Baseline characteristics of midwifery practices will include number of midwives working in the practice, number of clients per year, proportion of nulliparous and multiparous women, and rate of referral to secondary/tertiary care. Maternal baseline characteristics will include ethnic background, maternal age, educational level, height and weight, smoking, alcohol use, drug use, and work status during pregnancy.

#### Primary outcome – severe adverse perinatal outcome

The primary dichotomous clinical outcome of the main study will be a composite measure of severe adverse perinatal outcomes up to 7 days after birth defined as one or more of the following:Antepartum, intrapartum or perinatal death occurring from 28 weeks of gestation onwardApgar score <4 at 5 min after birth;Coma, stupor or decreased response to pain up to 7 days after birth;Asphyxia, defined as cord blood arterial base excess of less than minus 12;Neonatal seizures defined as clonic movements which cannot be stopped by holding the limb, occurring on two or more occasions before 72 h of age;Assisted ventilation for more than 24 h via endotracheal tube initiated within 72 h after birth;Septicemia, ascertained by a positive blood culture;Meningitis, ascertained by positive cerebrospinal fluid culture;Bronchopulmonary dysplasia (BPD), defined as need for oxygen at a postnatal gestational age from 36 completed weeks as well as an X‐ray compatible with BPD;Intraventricular hemorrhage, defined as grade 3 or 4 and diagnosed by cranial ultrasound or at autopsyCystic periventricular leukomalacia (PVL), diagnosed by cranial ultrasound or at autopsy showing periventricular cystic changes in the white matter excluding subependymal and choroid plexus cysts;Necrotizing enterocolitis, defined as either perforation of intestine, pneumatosis intestinalis or air in the portal vein, diagnosed by X‐ray or surgery, or at autopsy.

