An alternative approach to detect IUGR fetuses comprises routine third trimester ultrasonography. A recent prospective cohort study (*n* = 3977) demonstrated that routine third trimester ultrasonography using estimated fetal weight or abdominal circumference approximately almost tripled the detection rate of SGA neonates (sensitivity = 57 %) [12]. Routine third trimester ultrasound screening may have other benefits, including the detection of structural fetal abnormalities, e.g. craniospinal abnormalities and urinary tract abnormalities, which become manifest late in pregnancy [13]. However, a meta-analysis of 13 randomized trials among low-risk pregnancies (*n* = 34,980) did not reveal beneficial effects of third trimester ultrasound screening on primary outcomes of perinatal mortality, preterm birth less than 37 weeks, Caesarean section rates, and induction of labor rates [14]. Two major shortcomings have been identified in these previous trials [14, 15]. First, previous trials had methodological shortcomings, e.g., most trials were underpowered to detect clinically significant differences in severe perinatal outcomes, heterogeneity in number and timing of ultrasound scans, and contamination, i.e., ultrasound scans were often also conducted in the control group [14, 15]. Secondly, in many trials only the ultrasound screening procedure was described but not the use of subsequent management/intervention procedures when IUGR is suspected. If not coupled with an effective intervention, ultrasound screening alone cannot be clinically effective [12]. Moreover, ultrasound technology used in most previous trials is now outdated [14, 15]. Reviews on the effects of routine third trimester ultrasound screening on pregnancy and perinatal outcome concluded that a large-scale trial with adequate power is needed to address severe adverse perinatal outcomes and to examine long-term neurodevelopmental outcome in the offspring [14, 16].

Introducing a screening program can have negative consequences, such as unnecessary medical care [17]. Defining IUGR based on a certain cut-off, e.g., the lowest 10th percentile of estimated fetal weight, will probably not only lead to the detection of growth restricted fetuses but also to the classification of a group of ‘at risk fetuses’ who are constitutionally small and healthy. This may lead to unnecessary interventions, such as elective induction of delivery.

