Moreover, additional third trimester ultrasonography may affect maternal emotions, either positively in that negative screening results may be reassuring, or negatively in that it may increase maternal emotional distress, i.e., anxiety or depressive symptoms. Women may experience higher levels of emotional distress, due to an (incorrect) indication of IUGR and be exposed to additional monitoring and obstetric interventions [18, 19]. Experiences of maternal emotional distress due to positive, unexpected or unclear findings based on fetal ultrasound screening may continue into the postpartum period, even when abnormal screening results have not been confirmed by subsequent examinations [20–22].

In the case of positive screening results routine third trimester ultrasonography may particularly be related to the experience of moral dilemmas by pregnant women and professionals performing ultrasonography. For example, parents may find this burdensome due to increased responsibility that comes with the fact that they have to choose for further examinations of the fetus (or not). Professionals may find it difficult how to decide how much and which information they should provide to women/parents and when to advice referral for further clinical management [20–23].

Despite the lack of evidence for its clinical effectiveness [14, 15], routine third trimester ultrasound screening is increasingly used in midwifery care in the Netherlands, which results in a considerable rise in health care costs. Few former studies evaluated the cost-effectiveness of ultrasound scans [24, 25]. Although costs of the ultrasound examination itself have previously been investigated, we know little about resulting costs (e.g., costs associated with subsequent counselling, follow-up examinations, and subsequent interventions). So far, only one previous trial, The Helsinki ultrasound trial, addressed this matter showing that one-stage second-trimester ultrasound screening is cost-effective in reducing perinatal mortality as compared to care as usual when taking all significant costs and effects into account [25]. Moreover, the cost-effectiveness of routine third-trimester ultrasound screening combined with serial fundal height measurements and clinically indicated ultrasonography as compared to care as usual (CAU), i.e. serial fundal height measurements and clinically indicated ultrasonography alone, has not been studied earlier.

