#### Process measures

To evaluate the uptake of the intervention and the adherence to the consensus-based IRIS study protocol for the detection and management of IUGR, a number of process measures will be assessed, including the rate of women declining participation, the proportion of protocol violations, proportion of disagreements in primary outcomes based on reassessments by research assistants/nurses, and opinions of midwives on (in)effective elements of the intervention. Data on protocol adherence will be collected via standardized forms filled out by a researcher attending several multidisciplinary case evaluations or audits in case of perinatal deaths or severe adverse perinatal outcome. Protocol adherence will also be assessed via standardized case report forms filled out by research assistants/nurses using hospital records of a subsample of neonates and women (n ~ 2000) displaying perinatal/postpartum morbidity/mortality (for more detail see subsection data collection). Using a short questionnaire, we will evaluate community midwives’ experience of cooperation with healthcare professionals in secondary care in terms of the IRIS study protocol after the completion of the inclusion period.

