#### Existing medical databases/registries

For the main study (*n* = 15,000), data will be extracted from the following existing databases: 1) the database of the Perinatal Registry of the Netherlands (Perined); 2) ultrasound centers’ databases; 3) hospital medical records of mothers and neonates if applicable. These databases will be used to collect data on (primary) clinical outcomes, obstetric variables, ultrasound scans, and care processes.

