#### Hospital medical records

Using standardized case report forms research assistants/nurses will collect detailed information from approximately 2000 hospital medical records on healthcare utilization by and clinical outcomes of: 1) neonates who were referred to a pediatrician for neonatal admission, had a birth weight <5th percentile or a severe adverse perinatal outcome, e.g. Apgar score 5 min after birth <4, as indicated in the Perined database; and 2) women participating in the survey and being referred to a gynecologist/secondary care during the perinatal period, and women having a neonate who has been referred to a pediatrician, has a birth weight <5th percentile or a severe adverse perinatal outcome. The standardized case report forms will also be used to collect information on professionals’ adherence to the multidisciplinary consensus-based IRIS study protocol for the detection and clinical management of IUGR. By focusing on this group of neonates and women, we are able to efficiently collect data on severe adverse perinatal outcome, maternal perinatal morbidity, healthcare utilization, and protocol adherence which would not have been feasible in all 15,000 women.

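### The asphyxia item of the primary composite can be counted only where cord blood was sampled, and sampling may be more frequent in the intervention condition

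*Protocol article*

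**What the plan says.** The protocol article (Primary outcome – severe adverse perinatal outcome) defines "a composite measure of severe adverse perinatal outcomes up to 7 days after birth". It is met by any one of twelve items, one of which is "Asphyxia, defined as cord blood arterial base excess of less than minus 12". That item has no accompanying clinical criterion. The article gives no rule on which births have cord blood taken or on how an unsampled birth is counted.

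Outcome data come from three sources (Existing medical databases/registries): the national perinatal registry, ultrasound centres' databases, and hospital records where applicable. Detailed record review (Hospital medical records) covers about 2000 records. On the neonatal side it takes in "neonates who were referred to a pediatrician for neonatal admission, had a birth weight <5th percentile or a severe adverse perinatal outcome", the last as indicated in the registry. The reason given is that it yields data "which would not have been feasible in all 15,000 women".

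On what screening may do to care, the Background says of a fixed size cut-off that "This may lead to unnecessary interventions, such as elective induction of delivery". It adds that women with a possibly incorrect indication of growth restriction may "be exposed to additional monitoring and obstetric interventions". In both conditions suspected growth restriction is followed by the consensus-based management protocol (Care in the intervention and control group). Place of birth is listed as a secondary outcome.

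**The concern.** A neonate with a base excess of -13 and no other listed item is an event if the cord was sampled and, presumably, a non-event if it was not. If the chance of sampling depends on the care pathway, and the pathway depends on the allocated condition, the two conditions are measured with different sensitivity.

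The trial's own logic makes this plausible. The women are low-risk and in primary midwifery care. Screening is introduced to raise the detection of small fetuses; the Background cites a cohort in which detection almost tripled. Suspicion then triggers the management protocol, which sub-study A designs for collaboration between primary and secondary or tertiary care. More women followed up in this way could mean more sampled births in the intervention condition.

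Record review adds a smaller exposure. One of its routes, paediatric referral for admission, is a care decision made after allocation.

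The primary outcome is expected in 1.54% of women, so a small difference in ascertainment is not negligible against a planned difference of 0.54 points. The bias would run against screening. Neither intention-to-treat analysis nor adjustment for the listed confounders corrects a test result that was never obtained.

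**Working it through.** **1. The plan's own figures.** Inputs from Sample size of the trial: 1.54% versus 1.0%, 80% power, significance level 0.05, ICC 0.0003, cluster size 250.

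- A pooled two-proportion formula, two-sided, gives 6,749 per group, or 13,498 in total. The article states 13,536 (0.3% apart).
- Design effect: 1 + (250 − 1) × 0.0003 = 1.0747. Then 13,536 × 1.0747 = 14,547, as stated.
- At 15,000 women the effective number per condition is 7,500 / 1.0747 = 6,979, and power is 81.3%.

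The sample size reproduces. The point is about measurement, not arithmetic.

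**2. Which items depend on extra testing.** Death and a 5-minute Apgar score below 4 do not. Ventilation, seizures, bronchopulmonary dysplasia and similar items involve illness that would probably lead to paediatric care in either condition (an inference). Culture- or imaging-based items may be slightly exposed. The base-excess item is the most exposed, because a well neonate can meet it.

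**3. Size, on assumed inputs.** The documents give none of these three:

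- m, the share of women whom screening moves to hospital birth: 3–8%
- d, the difference in sampling between hospital and primary-care births: 50–85 percentage points
- q, the prevalence of base excess below -12: 1%

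Spurious excess in the intervention condition = m × d × q.

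- Lower: 0.03 × 0.50 × 1% = 0.015 points; 0.015 / 0.54 = 3%.
- Upper: 0.08 × 0.85 × 1% = 0.068 points; 0.068 / 0.54 = 13%.

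Both are gross figures. Neonates who would also count through death, Apgar score, seizures or ventilation should be deducted, and the documents give no overlap.

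**4. Effect on the test.** The excess is added to the 1.0% target and compared with 1.54%, with 6,979 effective women per condition.

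| Excess (points) | Observed intervention rate | Power |
|---|---|---|
| 0 | 1.000% | 81.3% |
| 0.015 | 1.015% | 78.9% |
| 0.068 | 1.068% | 69.1% |

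With no true effect (1.54% in both conditions), the chance of a significant result against screening rises from the nominal 2.5% to 3.0% at the lower and 5.1% at the upper excess. These figures use the article's simple design effect and ignore the period structure of the stepped wedge.

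**5. Can the existing safeguards detect or remove it?**

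- The registry covers all women but cannot hold a value that was never measured.
- Review of records below the 5th birth-weight percentile, or flagged in the registry, cannot recover an untaken sample.
- The process measure "proportion of disagreements in primary outcomes based on reassessments by research assistants/nurses" compares sources for recorded outcomes. It does not show which births were unsampled.

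**The case against.** The strongest reply is that nothing in the article says screening increases cord sampling or paediatric referral. The Background says only that it may lead to more monitoring and intervention, place of birth is an outcome still to be observed, and the management protocol is not shown. This stands. A reader might infer that events will be found more often under screening; the documents support only that they could be.

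Second, record review is not selected by referral alone. Birth weight below the 5th percentile and a registry-flagged outcome also qualify, and the criteria are the same in both conditions. Reassessment can also remove registry-coded events, so the net direction of this part is not established. This stands too, and it makes record review the lesser part of the point.

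Third, the size is built on assumptions. A reader might take a prevalence of 2% and arrive at 0.08 × 0.85 × 2% = 0.136 points, or 25% of the planned difference. That is hard to reconcile with the article: at 2%, sampling 77% of births (1.54 / 2) would make this item alone as frequent as the whole expected composite. Even 1% is generous, since with full sampling it would be about two thirds of 1.54%.

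Fourth, sampling practice and sensitivity analyses are often left to the full protocol or the analysis plan, and each element of the composite is already a separate secondary outcome. The silence on sampling is therefore not evidence that births go unsampled. The endpoint definition, however, is stated in the article and depends on a test. Reporting the elements separately does not give the composite without base excess, because one neonate can meet several items.

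**Conclusion.** The point holds as a conditional risk. The asphyxia item is met on a cord-gas value alone, the article does not say that every birth is sampled, and the pathway it describes makes more frequent sampling in the intervention condition plausible. The direction would be against screening. The documents do not establish that the bias is present, and its size cannot be obtained from them.

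On the assumptions shown, it is 0.015–0.07 percentage points, or 3–13% of the planned difference, before deducting overlap with other items. The low end is minor. The high end would lower power from 81.3% to about 69%, enough to justify an inexpensive safeguard but not a change to the primary endpoint.

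**What to change.** Keep the primary definition. Then:

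- Pre-specify the composite without the base-excess item as a key sensitivity analysis of the primary outcome, using the same multilevel logistic model.
- Report by condition the proportion of births with a cord-gas result, as far as the data sources record it.
- Report by condition the proportion of neonates whose hospital record was reviewed.

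If the two analyses agree and the proportions are similar, the concern can be set aside; if not, readers can judge how far ascertainment may explain the result.

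The cost is a little extra analysis, and the sensitivity analysis has fewer events and so less precision. The article does not show that the registry records whether a cord gas was taken, so that proportion may be incomplete. Adding a clinical sign to the asphyxia item is not recommended: it would lower the event rate and upset the 1.54% on which the sample size rests.

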#### Primary outcome - costs

Healthcare costs will include costs related to pregnancy-related healthcare use, including community midwife consultations, referrals to specialist care, ultrasound examinations, laboratory tests, CTG monitoring, hospital admission, interventions during labor, and admission to neonatal unit. Healthcare costs will be calculated using standard costs published in the Dutch costing guidelines [28]. Medication use will be calculated using prices of the Royal Dutch Society for Pharmacy.

Absenteeism and presenteeism at work (indirect costs) as reported by (pregnant) women will be assessed by the iMTA Productivity Cost Questionnaire (iPCQ) [29].

The friction cost approach will be used to estimate indirect costs using Dutch age and sex specific lost productivity costs [30, 31].

#### Secondary outcome measures- composite outcome

Two other dichotomous composite outcomes are defined as secondary outcomes. The first is spontaneous vaginal birth without intervention, i.e., a birth without any of the following interventions: 1) induction of labor other than amniotomy, 2) vacuum/forceps assisted birth, 3) Caesarean section; 4) augmentation of labor; and 5) pharmacological pain relief.

Secondly, another secondary dichotomous composite outcome is maternal perinatal morbidity/mortality, defined as the presence of one or more of the following: 1) maternal death within 42 days after giving birth, 2) hypertension, 3) pre‐eclampsia, 4) postpartum hemorrhage larger than 1000 mL, and 5) third or fourth degree perineal trauma.

#### Secondary outcomes – single outcomes

Single outcomes include the different elements of the composite primary outcome and the secondary composite outcome. Other secondary single outcomes will be neonatal mortality and severe morbidity between the 7th and 28th day after birth, congenital abnormalities, life threatening congenital conditions among neonates, non‐cephalic presentations (when labor started) in primary care, and place of birth. Mean birth weight, low birth weight, macrosomia, mean gestational age, and prematurity will also be single secondary outcomes.

Other secondary single outcomes, that will be reported by women participating in the survey (*n* = 1500), will include 1) maternal prenatal and postnatal quality of life (EQ‐5D‐5 L and one item of the short form health survey (SF-36) [32–34]); 2) maternal experience of continuity of healthcare and satisfaction with healthcare during pregnancy and delivery (Nijmegen Continuity Questionnaire (NCQ) and Pregnancy and Childbirth Questionnaire (PCQ)) [35, 36]; 3) maternal pre- and postnatal anxiety and pregnancy-specific anxiety (State and Trait Anxiety Inventory (STAI) [37], and the Pregnancy Anxiety Questionnaire-Revised (PRAQ-R)) [38]; 4) and pre- and postnatal depressive symptoms (Edinburgh (Postpartum) Depression Scale) [39, 40]; and 5) prenatal and postnatal maternal bonding, i.e., the emotional tie between the mother and the (unborn) child (Maternal Antenatal Attachment Scale (MAAS) and Maternal Postnatal Attachment Scale (MPAS)) [41, 42]. Moreover, other secondary single outcomes will be infant developmental milestones at age 6 months assessed with the Ages and Stages Questionnaire (ASQ) and toddlers’ behavioral problems and developmental milestones at 24 months measured via the Child Behavior Checklist (CBCL) and ASQ, respectively [43–45].

In a purposively selected subsample of pregnant women (n ~ 15) participating in the intervention group, semi-structured interviews will be conducted during late pregnancy to explore and better understand the role of third trimester ultrasound screening in the experience of maternal pregnancy-specific anxiety and maternal bonding.

